### Cognitive Rehabilitation Programs

Both the CoRe and HomeCoRe are research software tools developed within a long-lasting collaboration between clinicians from the IRCCS Mondino and bioengineers from the University of Pavia. At the moment, the tools are limited to Italian speaking participants. The tools allow a participant-tailored intervention aimed at stimulating several cognitive abilities (e.g., logical-executive functions, attention/processing speed, working memory, and episodic memory) through a series of sessions of exercises (see Table 2 for details). Their use is time-saving for the therapists, as they are ready to use and do not require a continuous manual setting of exercises for each training session. This is because, once the therapist has remotely set up the treatment plan, exercises take place in an adaptive mode across all the sessions. In particular, during their dynamic generation, performance data of an individual participant are analyzed in order to set the appropriate difficulty level. Performance data of the participants refer to the response accuracy normalized according to the number of aids that the participant required to solve the task. Furthermore, for each exercise and each level, thresholds are defined to allow difficulty levels to progressively increase in order to stimulate neural plasticity (6, 45, 46). In addition, the system calculates an overall “Weighted Score” (WS), taking into account the correctness of the answers, the execution time, and the difficulty of the exercises. The WS informs the therapist about each performance of the participant in a single value. Hence, WS represents a useful and advantageous index that can be used to assess both the overall outcome of a training session and the global trend of the rehabilitation (see Figure 2).

**Table 2 T2:** CoRe/HomeCoRe description of tasks, reporting involved cognitive skills.

**Tasks**	**Description**	**Main involved skills**
* **Learning of word pairs** *	Pairs of words are shown on the screen, the participant is asked to rewrite the second word of the pair when it is shown	Long-term memory abilities; learning and re-enactment strategies; visual imagery
* **Word categorization** *	Words belonging to different categories are presented on the screen, the patient is asked to rewrite them in any order but respecting the corresponding category	Long-term memory abilities; learning and re-enactment strategies; visual imagery; categorical thinking
* **Puzzle** *	The participant is asked to put together the pieces of a figure to recompose it	Visuo-spatial long-term memory; visual imagery; mental representation and planning
* **Span backward** *	The participant is asked to write the numbers in a reverse order compared to what previously heard	Verbal working memory; processing-speed
* **Memory** *	After a study phase in which all cards are shown face up, they are faced down. The participant is asked to recall and match all equal cards in the least number of tries, by turning over pairs of cards one by one	Long-term memory abilities; visuo-spatial abilities
* **Visuospatial matrices** *	The participant receives a sequence of spatial information (e.g., right, left, up, down) and then he/she is asked to store it and reproduce in the correct order on a grid	Working memory; visuo-spatial abilities; processing-speed
* **Logical sequences** *	A sequence of images is shown, the participant is asked to select, among several options, the one that completes the series	Non-verbal reasoning; mental problem solving; decision making
* **Image and sound** *	The participant is asked to evaluate right or wrong matching between visual (image size) and auditory (sound volume) stimuli	Inhibitory control; processing-speed; working memory
* **Sentence recomposing** *	The participant is asked to put scrambled words in the correct order to form a full sentence	Mental and verbal planning; conceptual abstraction abilities
* **Story recomposing** *	The participant is asked to reorganize a scrambled sequence of images in the right chronological order to form a short story	Planning of activities: problem solving; temporal sequencing; visual attention
* **Recognition exercise** *	The participant is asked to identify and select specific items within a matrix of random elements (letters or numbers)	Sustained and selective attention; visuo-spatial scanning; processing-speed

**Figure 2 F2:**
[figure not shown]
Therapist interface for monitoring performances of the participant in terms of overall Weighted Score (left) and interface of the participant for the execution of exercises (right).

### CoRe/HomeCoRe Software Architecture

Both the CoRe and HomeCoRe require a personal computer equipped with a touch screen. HomeCoRe is installed on a laptop (password protected and encrypted) that is supplied to participants by the therapist, while CoRe is installed on a desktop PC located in the hospital setting. Both the HomeCoRe and CoRe will be installed on the personal computer by an expert engineer and under the supervision of the Information Technology (IT) department—IRCCS Mondino. CoRe, being an in-person treatment, will be then performed under therapist monitoring; HomeCoRe, being home based, will/could be performed under caregiver monitoring. In particular, before the beginning of HomeCoRe treatment, participants and possible caregivers will be trained together at the hospital on the use of the rehabilitation tool at home. This is in order to account for possible differences in baseline technological skills. Then, during the training sessions, participants, with the possible support of their caregivers, will go through each exercise of the treatment until they feel familiar with the use of the device. During the rehabilitative program at home, remote technical support will be available when requested. To this aim, participant will be provided with the support team contacts. The treatment sessions, both in the CoRe and HomeCore, can be paused in case of fatigue of the participant and resumed at a later time.

Differently from CoRe, HomeCoRe architecture includes two main components, namely, therapist side and participant/caregiver side and a communication system (HomeCoRe server). The therapist-side dashboard allows remotely setting and monitoring all the parameters of the treatment plan (e.g., frequency and duration of the plan, type of exercises, difficulty level). The interface of the participant/caregiver is very simple and it allows to view/execute the exercises of the day and to send the results to the therapist (see Figure 3).

**Figure 3 F3:**
[figure not shown]
Home page of the therapist side of the interface for setting the requirements for the exercise plan (left) and home page of the participant/caregiver side of the interface (right) for HomeCoRe.

The HomeCoRe system can be used online or offline in the case that the internet connection of the participant is not available. In the online mode, the communication between the therapist side and participant side takes place automatically through a dedicated communication protocol managed by the HomeCoRe server, while in the offline modality, some manual operations are required for loading the therapeutic plan offline and save result report on an external memory support (e.g., USB key or hard disk). In any case, the communication with the therapist is asynchronous.

### Outcome Measures

As the primary outcome measure, we will consider the change in global cognitive functioning, measured using the MMSE at T1 compared to T0. Secondary outcome measures will be longitudinal changes in all the neuropsychological tests, questionnaires and scales (T1, T2, and T3 vs. T0 when applicable according to Table 1). Secondary outcome measures will include also participant-centered outcomes to assess those aspects that are most important for the participants and the subjective evaluation of intervention success at T1.

### Statistical Analysis

#### Sample Size Calculation

Sample size has been estimated based on previous evidence in the literature (47). Since this is a non-inferiority study, we will consider as margin *d* a value of two points difference (T1 vs. T0) at the MMSE between the two groups. We predict to obtain a mean difference between HomeCoRe and CoRe groups of about one point at the MMSE with an SD of 1. Considering an alpha significance of 0.05 and a power of 0.9, the sample size for a non-inferiority study is 18 participants per group, for a total of 36 participants. It is planned to enroll a total of 40 participants in order to account for possible dropouts. If dropout rates between T0 and T1 will be higher than expected, extra participants will be recruited. The sample size for non-inferiority studies was calculated using R 4.0.2 software, SampleSize4ClinicalTrials package.

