### Participants and Eligibility Criteria

Participants will be recruited from the Dementia Research Center outpatient services and Neurorehabilitation Unit of the IRCCS Mondino Foundation (Pavia, Italy) and screened for eligibility criteria through a clinician evaluation made by an expert neurologist.

The inclusion criteria for participants will be:

Diagnosis of Mild or Major Neurocognitive Disorders based on the DSM-5 (5)Aged between 60 and 85 yearsYears of education ≥ 5Clinical Dementia Rating (CDR) (30) score = 0.5–1.

The exclusion criteria will be:

Mini-Mental State Examination (MMSE) score <20Presence of cognitive impairment secondary to an acute or general medical disorder (e.g., brain trauma or tumor)Presence of severe neuropsychiatric conditions (e.g., mood and behavioral disorders)Presence of severe sensory disorder (e.g., deafness or blindness) or motor impairment that prevent trunk control and/or sitting positionCurrent cognitive treatmentsLack of family support for participants with Major Neurocognitive Disorder

Medication intake for dementia and/or past cognitive rehabilitation treatments will be not considered as exclusion criteria given that these factors are not expected to affect the outcome of this study. Any pharmacological treatment ongoing must be stable across the entire period of this study protocol.

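### The 90% power is conditional on an SD of 1 for individual MMSE change, and the baseline-covariate rule leaves some available precision unsecured

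*Protocol article*

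**What the plan says.** The primary outcome is "the change in global cognitive functioning, measured using the MMSE at T1 compared to T0" (Outcome Measures). The margin is "a value of two points difference (T1 vs. T0) at the MMSE between the two groups", and the planning difference is "of about one point at the MMSE with an SD of 1" (Sample Size Calculation). With "Considering an alpha significance of 0.05 and a power of 0.9", the article concludes that "the sample size for a non-inferiority study is 18 participants per group, for a total of 36 participants". Forty are to be enrolled to allow for dropout, and further recruitment is foreseen only if dropout before T1 is higher than expected. One literature source is cited for the calculation, and no figures from it are shown.

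The eligible population is "Diagnosis of Mild or Major Neurocognitive Disorders based on the DSM-5", with a CDR of 0.5 to 1 and MMSE scores below 20 excluded (Participants and Eligibility Criteria). Randomization is stratified by diagnosis.

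Under Planned Analysis, demographic and clinical characteristics (diagnosis among them) and T0 scores are treated as covariates in their role as possible between-group differences. The article does not say that the primary comparison is adjusted for baseline MMSE in every case.

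**The concern.** The required sample size grows with the square of the SD, so this one input carries most of the power claim. The outcome is the difference between two MMSE administrations, in a sample that spans two diagnostic categories and scores from 20 upward. Under those conditions an SD of 1 is a demanding value. It makes the margin two full SDs of the outcome and the predicted gap one full SD. If the real SD is moderately larger, the likeliest result is a confidence interval too wide to establish non-inferiority.

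The second part concerns the analysis. Baseline MMSE is measured on everyone and will correlate with T1 MMSE, so adjusting for it reduces the residual variance. If T0 scores enter the model only when the groups look different, that reduction depends on the observed data, and so does the form of the primary model.

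**Working it through.** **Inputs from the article.** Margin 2, planning difference 1, SD 1, alpha 0.05, power 0.9, 18 per group. The article gives neither the direction of the difference nor the sidedness of alpha. The stated sample size is reproduced with a 1-point deficit for HomeCoRe (2 − 1 = 1 point of room) and a one-sided 0.05.

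**Step 1: reproduce the plan's figure.**
n per group = 2 × SD² × (z₀.₉₅ + z₀.₉₀)² / (margin − difference)² = 2 × 1² × (1.645 + 1.282)² / 1² = 17.1, rounded up to 18. This matches. Here SD is the SD of one participant's change, so the calculation settles what the SD of 1 refers to even though the sentence is loose. At one-sided 0.025 the same inputs give 22.

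**Step 2: vary only the SD.** Power comes from a noncentral t with 34 df and noncentrality 1 / (SD × √(2/18)) = 3 / SD. SDs above 1 are assumptions.

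| SD of change | Power, 18 per group, one-sided 0.05 | Power, one-sided 0.025 | n per group for 90% (one-sided 0.05) |
|---|---|---|---|
| 1 | 90% | 83% | 18 |
| 1.25 | 76% | 64% | 27 |
| 1.5 | 62% | 49% | 39 |
| 2 | 43% | 31% | 69 |
| 2.5 | 32% | 21% | 108 |

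The n for SD 1.25 is 17.13 × 1.25² = 26.8, rounded up. If all 40 enrolled are evaluable (20 per group), power at SD 2 is 46%.

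**Step 3: vary the true difference.** If it is 0, the room to the margin is 2 points and the noncentrality is 6 / SD. At SD 2 this equals 3, the same as in the plan's own case, so power is again 90%.

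**Step 4: what an SD of 1 requires.** With equal between-person SD s at T0 and T1 and correlation r, SD(change) = s × √(2(1 − r)). Setting this to 1 gives r = 1 − 1/(2s²):
- s = 2: r = 0.875
- s = 2.5: r = 0.92
- s = 3: r = 0.944

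The article gives neither s nor r. At an assumed r = 0.8, the change SDs for these three values of s are 1.26, 1.58 and 1.90.

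**Step 5: what baseline adjustment adds.** The residual SD under ANCOVA is s × √(1 − r²). At r = 0.8 this is 0.6 × s. Power is for 18 per group, a 1-point deficit and one-sided 0.05.

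| s | SD of change | ANCOVA residual SD | Power, unadjusted change | Power, ANCOVA |
|---|---|---|---|---|
| 2 | 1.26 | 1.20 | 75% | 79% |
| 2.5 | 1.58 | 1.50 | 58% | 62% |
| 3 | 1.90 | 1.80 | 46% | 50% |

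The gain is about 3 to 4 points in each row. Using 32 df for the two added covariates changes these powers by about 0.1 point. Any further gain from the diagnosis stratum is not counted.

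**The case against.** The strongest reply is that no error has been shown. The sample size follows from its inputs, and the article attributes the calculation to a published source that is not available here and may support an SD of 1. A wide spread between participants does not by itself produce a large SD of change, because stable differences cancel between T0 and T1. The CDR restriction and the MMSE floor narrow the spread, and the correction of scores for age, sex and education may narrow it further. Correlations of 0.88 to 0.94 over a six-week programme are not shown to be implausible. All of this stands, and it is why the point is about sensitivity.

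A reader might infer from the 43% that the trial is badly underpowered. The article does not support that. An SD of 2 lies above the 1.26 to 1.90 derived at r = 0.8, and reaching it would need r of 0.50, 0.68 or 0.78 for s of 2, 2.5 or 3. The 43% also assumes that HomeCoRe is truly 1 point worse. The study hypothesis is comparable benefit, and with no true difference power at SD 2 is about 90%. Against this, the 1-point difference is the plan's own planning value, so the power it quotes has to be judged there.

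A reader might also infer that the SD of 1 could belong to the group difference and not to individuals. The wording allows that reading, but the reproduced sample size does not.

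Finally, a journal article need not print a table of power by SD, and its supplementary analysis plan is not shown. The absence of a table is therefore not an error. The covariate rule is different, because the article states it.

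**Conclusion.** The stated 90% power is correct for its inputs and fragile outside them. At the plan's own 1-point deficit and one-sided 0.05, a change SD of 1.25 lowers it to about 76% and an SD of 1.5 to about 62%; at SD 2 it is about 43%. The SDs above 1 are assumptions, and the article neither confirms nor contradicts the value of 1. If the true difference is nearer 0, the loss is much smaller.

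The covariate rule is a separate and firmer point. As described, it makes adjustment for baseline MMSE depend on group differences and so leaves a small, free gain in precision unsecured. That gain, about 3 to 4 percentage points at r = 0.8, would not make up for a large error in the SD. At SD 2, 90% power would still need 69 per group.

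**What to change.** 1. Prespecify the primary non-inferiority comparison as an ANCOVA of T1 MMSE (or of change) on group, always adjusted for T0 MMSE and the diagnosis stratum, whatever imbalance is observed. Both variables are already collected, so this costs only wording. It also removes a covariate choice that depends on the data.
2. In the sample size paragraph, state that the SD of 1 is that of individual T1–T0 change, that alpha is one-sided, and that the 1-point difference is a deficit for HomeCoRe, if those are the intended readings.
3. Present the power of 0.9 as conditional on that SD, with a short table over plausible values such as the one above. The Introduction reports that CoRe has already been tested in early cognitive decline, so the sponsor's own change data would be the best guide to the range.

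Items 2 and 3 need a few sentences and one table. They make the power statement less favourable but more informative. None of the three requires additional participants, and none would restore 90% power if the SD proved to be well above 1.

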#### Planned Analysis

Statistical analysis on outcome measures will be conducted using the SPSS software (see Supplementary Materials for planned analysis). A normality test will be used to assess the distribution of all the outcome measures. Baseline differences between groups will then be tested using the independent samples *t*-test for parametric data and the Mann–Whitney *U*-test for non-parametric data. Within-group statistical tests will be performed for both the CoRe and HomeCoRe groups to look for significant changes in primary and secondary outcome measures over time. Between-group tests will be performed to look for differences in primary and secondary outcome measures between HomeCoRe and CoRe participants. Possible between-group differences in demographic and clinical characteristics (e.g., age, sex, years of education, diagnosis, and cognitive reserve) and in T0 scores in primary and secondary outcome measures will be considered as possible confounders and will be treated as covariates in the analysis. *p* ≤ 0.05, corrected for multiple comparisons, if appropriate, will be considered as statistically significant.

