Despite the interesting potentialities of TR, several issues are slowing its integration into the clinical routine. A major issue is the poor technological skills of older adults, which may result in difficulties in managing technological devices autonomously (9). Therefore, platforms should be accessible and user-friendly; duration and frequency of rehabilitation activities should vary according to characteristics of the patients (10); therapists should monitor adherence to treatment and outcome of the rehabilitation process remotely (11). There is some evidence (12–17) exploring the usability and acceptability of Information and Communication Technologies (ICTs) in elderly care including participants with dementia or MCI and giving some recommendations for designing interfaces for this kind of users. In general, it resulted that these systems were enjoyable and feasible for participants even if usability not always was high.

However, randomized controlled trials (RCTs) investigating TR efficacy compared to the traditional in-person approaches are still scanty (4). Recently, this topic has gained growing interest, due to the challenges faced by the healthcare systems during coronavirus disease 2019 (COVID-19) pandemic (18–22).

During the past years, we implemented the software CoRe for in-person cognitive training in the hospital setting supervised by a trainer (23, 24). CoRe has been successfully tested in terms of usability and immediate and long-term effectiveness in participants with early cognitive decline (25–27). In light of the improvement in telemedicine approaches and in view of the willingness of treated participants and caregivers to start/continue CoRe program at distance (28), we have developed the “home” version of CoRe (i.e., HomeCoRe) supporting cognitive intervention remotely (29) with the assistance of a family caregiver.

This longitudinal RCT study, thus, aims to evaluate and compare the effectiveness of HomeCoRe and CoRe programs in participants with MCI or mild dementia. Our hypothesis is that cognitive TR delivered via HomeCoRe provides benefits that are comparable to the in-person version of the program on cognitive and behavioral functioning and on additional participant-centered outcomes.

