## Methods and Analysis

### Study Design

This study is a prospective single-blind randomized controlled non-inferiority trial. The Consolidated Standards of Reporting Trials (CONSORT) flowchart for enrollment and randomization is shown in Figure 1. After recruitment, participants will be contacted and will undergo in-person baseline assessment (T0) using the below-listed tests (see evaluation of the participants section and Table 1). Participants who meet the inclusion criteria will be enrolled and randomized to one of two groups: HomeCoRe and CoRe. For both the groups, the intervention will consist of a 6-week program (3 sessions/week, each lasting ~45 min). Follow-up in-person neuropsychological assessments will be scheduled at the end of the rehabilitation program (T1) and after 6 (T2) and 12 months (T3).

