## Discussion

Due to the increase of the aging population, we are witnessing a steady increase in the number of older adults at risk of developing cognitive decline with a consequent increase of economic burden on healthcare. Therefore, the WHO Global Action Plan on the Public Health Response to Dementia 2017–2025 recommends taking global action against cognitive decline and dementia, encouraging governments worldwide to focus on prevention and improving healthcare services (48). Telemedicine is defined as an interface in a virtual patient–clinician relationship to provide primary and secondary care by adopting innovative solutions reaching larger groups of participants (49). Telemedicine can be considered as an adaptation of the healthcare model based on in-person interaction, according to the characteristics and needs of the participants (50). In particular, TR is a telemedicine subfield aimed at providing rehabilitation at a distance (51). TR provides benefits for the healthcare system, patients, and caregivers in terms of cost-effectiveness and feasibility for large-scale implementations (52–54). It represents a replacement for in-person treatment or its continuation, favoring equitable access to care not only for older patients with dementia or physical disabilities, but also for subjects of working age or living in geographically remote areas in predementia phases. Hence, TR is a unique opportunity in the field of cognitive rehabilitation to guarantee constancy and continuity to cognitive training programs.

The results of this trial will inform about the comparability of HomeCoRe with CoRe system. In case they will result equivalent, such a finding would support the use of HomeCoRe in the treatment of patient at distance, with the consequent multiple positive impacts mentioned above. In this framework, HomeCoRe could be incorporated into clinical routine practices as a complementary non-pharmacological therapy to contrast cognitive impairment and dementia. In case HomeCoRe will prove less effective than CoRe, it would lead to the conception of telerehabilitation as a compromise that must be made under particular conditions such as in case of emergency [i.e. coronavirus disease 2019 (COVID-19) pandemic] or personal needs (e.g., travel difficulties).

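### The Planned Analysis section tests the primary outcome for a difference at p ≤ 0.05 and does not use the 2-point margin on which the trial is designed and sized

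*Protocol article*

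**What the plan says.** The Study Design section fixes the framework: "This study is a prospective single-blind randomized controlled non-inferiority trial". Outcome Measures names the endpoint: "As the primary outcome measure, we will consider the change in global cognitive functioning, measured using the MMSE at T1 compared to T0". Sample Size Calculation sets the margin, "we will consider as margin *d* a value of two points difference (T1 vs. T0) at the MMSE between the two groups", and the planning assumption, "We predict to obtain a mean difference between HomeCoRe and CoRe groups of about one point at the MMSE with an SD of 1". With alpha 0.05 and power 0.9 it arrives at 18 participants per group, 36 in total, with 40 to be enrolled.

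Planned Analysis describes something else. After baseline comparisons and within-group tests it says: "Between-group tests will be performed to look for differences in primary and secondary outcome measures between HomeCoRe and CoRe participants". The primary outcome is expressly included. The criterion given is a p-value of at most "0.05, corrected for multiple comparisons, if appropriate, will be considered as statistically significant". The section mentions neither a confidence limit nor the margin, and it refers to Supplementary Materials for the planned analysis.

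On interpretation, the Introduction hypothesises that HomeCoRe "provides benefits that are comparable to the in-person version of the program on cognitive and behavioral functioning and on additional participant-centered outcomes". The Discussion says: "In case they will result equivalent, such a finding would support the use of HomeCoRe in the treatment of patient at distance". It sets this against the case where HomeCoRe proves less effective. The Abstract also speaks of equivalence.

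**The concern.** A non-inferiority claim needs the confidence limit for the treatment difference to exclude the margin. A test of zero difference answers another question. A non-significant result may only reflect imprecision, and a significant one may be a small deficit that the margin was set to tolerate. An analyst who followed the printed section would produce a p-value that does not settle the trial's hypothesis. The Discussion's two outcomes, equivalent or less effective, would then have no stated link to the margin. At stake is the primary conclusion.

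**Working it through.** **Inputs.** From Sample Size Calculation: margin 2, expected difference 1, SD 1, alpha 0.05, power 0.9, 18 per group. The section gives neither the direction of the expected difference nor the sidedness of alpha, so both are inferred by reproducing the sample size.

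**1. Reproduce the sample size.** n per group = 2 × [(z_alpha + z_power) × SD / (margin − deficit)]².
- One-sided 0.05, HomeCoRe 1 point worse: 2 × [(1.645 + 1.282) × 1 / (2 − 1)]² = 17.13, rounded up to 18. This matches the plan.
- One-sided 0.025: 2 × (1.960 + 1.282)² = 21.02, rounded up to 22 per group, or 44 completers.
- If the 1 point favoured HomeCoRe, the distance to the margin would be 3 and n = 17.13 / 9 = 1.9, so 2 per group. The stated 18 therefore implies a deficit for HomeCoRe.

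**2. Compare the two tests under those inputs.** The standard error of the difference is 1 × √(2/18) = 0.333, with 34 degrees of freedom. The predicted deficit lies midway between zero and the margin, 1 / 0.333 = 3 standard errors from each. By the non-central t distribution:
- Test against the margin, one-sided 0.05: succeeds in 90.2% of trials.
- Test for a difference, two-sided 0.05: significant in 83.0% of trials.
- Both together (non-inferior and significantly worse): about 73% of trials (simulation, 200,000 runs).

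**3. The predicted result observed exactly** (deficit 1, SD 1, 18 per group):
- 90% CI for the deficit: 1 ± 1.691 × 0.333 = 0.44 to 1.56.
- 95% CI: 1 ± 2.032 × 0.333 = 0.32 to 1.68.
- Difference test: t = 3.0, p = 0.005.

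Both intervals lie below 2, so the design criterion is met while the difference test is clearly significant.

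**4. The opposite direction.** Take a true deficit of exactly 2 points. The probability of a non-significant difference with 18 per group is:

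| SD of change | Source | Non-significant difference | Margin test wrongly passes |
|---|---|---|---|
| 1 | plan | about 0.006% | 5% |
| 2 | assumed | 17% | 5% |
| 3 | assumed | 51% | 5% |

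This error is negligible at the plan's SD. It becomes material only if the SD is two to three times as large.

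All figures are for an unadjusted comparison.

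**The case against.** The strongest objection is that Planned Analysis is a short paragraph covering all outcomes, and that it points to Supplementary Materials which are not shown. A margin-based primary analysis may be there, and what an article leaves to a fuller document is not missing. This limits the point: it can be said only that the printed article does not use the margin, not that the trial's analysis never does. It does not remove the point, because the article does more than stay silent. It states a test for differences that expressly includes the primary outcome, and a p-value criterion.

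A reader might also infer that the investigators will treat a non-significant result as non-inferior, or a significant one as failure. No section says so. Planned Analysis defines only statistical significance, and the Discussion does not say how equivalent or less effective will be judged. The contrast between those two outcomes stands only in the Discussion; the Abstract speaks of equivalence and of non-inferiority but not of HomeCoRe being less effective.

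Two further criticisms are tempting and are not made here. The absence of margins for secondary outcomes is ordinary in a non-inferiority trial. The effect of the multiplicity correction cannot be sized, because the plan corrects only if appropriate and names neither a method nor a family of tests.

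Finally, the plan allows covariate adjustment where groups differ, so the percentages are approximate for the analysis that would be run.

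**Conclusion.** The point holds for the article as printed: design and sample size rest on a 2-point margin, and the stated between-group analysis of the primary outcome is a difference test that does not use it. It should be corrected before analysis because it concerns the primary inference.

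The conflict is large on the plan's own inputs: the difference test is significant in 83% of trials where the margin test succeeds in 90%, and both occur together in about 73%. This rests on reading the 1-point difference as a deficit and alpha as one-sided, the reading that gives 18 per group. The risk of missing a deficit at the margin, 17% to 51%, depends on assumed SDs of 2 to 3. The documents do not support the stronger reading that low power would drive a false finding of comparability at the planned SD of 1.

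**What to change.** In Planned Analysis, state for the primary outcome that HomeCoRe is non-inferior if the lower limit of the two-sided 90% confidence interval for the covariate-adjusted difference (HomeCoRe minus CoRe) in T1–T0 MMSE change lies above −2. The level must be written down: 90% two-sided corresponds to the one-sided 0.05 that gives 18 per group. A 95% interval (one-sided 0.025) would need 22 per group, and those 44 completers exceed the 40 to be enrolled.

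Add that a non-significant difference will not be read as non-inferiority or equivalence, and that an interval crossing −2 means non-inferiority has not been shown. In the Abstract and Discussion, replace the equivalence wording with non-inferior on MMSE at T1. Report secondary outcomes as differences with confidence intervals, without claims of comparability based on non-significance. Reconcile the section with the Supplementary Materials.

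The cost is wording only. No new data are needed, and no more participants if one-sided 0.05 is kept.
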